## Abstract

**Background:**

Chronic kidney disease (CKD) is a rising public health problem that may progress to kidney failure, requiring kidney replacement therapy. It is also associated with an increased incidence of cardiovascular disease (CVD). Because of its asymptomatic nature, CKD is often detected in a late stage. Population screening for albuminuria could allow early detection of people with CKD who may benefit from preventive treatment. In case such screening is performed in a general practitioner (GP) setting, this will result in relatively high costs. Home-based screening might be an effective and cost-effective alternative.

**Aim:**

The THOMAS study (Towards HOMe-based Albuminuria Screening) is designed to prospectively investigate two methods for home-based population screening for increased albuminuria to detect yet undiagnosed CKD and risk factors for progression and CVD.

**Methods:**

This investigator initiated, randomized population-based study will include 15.000 individuals aged 45–80 years, who will be randomly assigned to be invited for a home-based screening test for albuminuria with a more conventional urine collection device or an innovative smartphone application. If the test result is positive upon confirmation (i.e., elevated albuminuria), participants are invited to a central screening facility for an elaborate screening for CKD and CVD risk factors. Participants are referred to their GP for appropriate treatment, if abnormalities are found. Primary endpoints are the participation rate, yield, and cost-effectiveness of the home-based screening and elaborate screening.

**Conclusions:**

The THOMAS study will evaluate the effectiveness and cost-effectiveness of home-based albuminuria screening in the general population for the early detection of CKD and CVD risk factors. It will provide insight into the willingness to participate in population screening for CKD and into the compliance of the general population to a corresponding screening protocol and compliance to participate. Thus, it may help to develop an attractive novel screening strategy for the early detection of CKD.

**Trial registration:**

ClinicalTrials.gov, registration number NCT04295889, registered 05 March 2020. https://www.google.com/search?client=firefox-b-d&q=NCT04295889.

## Introduction

Chronic kidney disease (CKD) is a public health problem with a rising global prevalence that currently exceeds 10% [1,2]. CKD may progress to kidney failure, requiring dialysis or transplantation [3]. Importantly, patients with CKD, even in the earliest stages, are at increased risk for cardiovascular disease (CVD) [4]. These sequelae result in an impaired quality of life, decreased life expectancy, and a high economic burden for society [3]. CKD often remains undiagnosed for a long time and therefore not treated [5]. Therefore, earlier identification of CKD is desired to allow a timely start of treatment to prevent progression and associated complications [6].

Traditionally, most attention to screen for CKD was focused on measuring kidney function. However, screening for impaired kidney function allows only late intervention. During the last two decades, it has become clear that increased albuminuria is a strong risk factor for progressive CKD. In addition, it also predicts CVD as a marker of generalized vascular endothelial damage [7–9]. In the PREVEND study, that was performed in 1997, 5.6% of the general population had confirmed elevated albuminuria (i.e., urinary albumin excretion (UAE) ≥ 30 mg/24h) [10]. In the majority of these subjects, elevated albuminuria was not known to these subjects nor their general practitioners (GP), and 79% of them also had hypertension, type 2 diabetes, or hypercholesterolemia. In 89% of these individuals, one of these comorbidities was not yet diagnosed. Additionally, it was found that screening for increased albuminuria identified patients with a preserved kidney function, but a more pronounced decline in estimated GFR (eGFR) thereafter [8], and a cardiovascular (CV) event rate twice as high as in normoalbuminuric patients with a similar CV risk factor profile [11].

Screening for albuminuria could thus provide an opportunity to detect people with early stage CKD who may benefit from preventive treatment. Therefore, population screening for albuminuria has been proposed. However, the cost-effectiveness of such a screening strategy has been questioned [12–14]. Of note, these screening programs in general were modeled as screening for severely elevated albuminuria (i.e., albumin-to-creatinine ratio (ACR) ≥300 mg/g, corresponding with a 24hr UAE ≥300 mg/24hr), with screening performed by physicians (e.g., GPs), and taking into account only benefit for prevention of kidney failure. When screening is performed this way, it will identify only a few subjects, the costs for screening will be high, and the potential benefits limited. Another screening strategy has therefore been proposed, i.e., a home-based pre-screening for moderately elevated albuminuria (i.e., ACR ≥30 mg/g, corresponding with a 24hr UAE ≥30 mg/24hr), with subsequent screening by GPs of only those with proven elevated albuminuria, and taking into account not only prevention of kidney failure but also benefits with respect to prevention of CVD. Such a screening strategy has been suggested to be cost-effective [15].

In recent years, albuminuria screening tests have become available making home-based population screening for elevated albuminuria feasible. The present paper describes the design and rationale of the Towards HOMe-based Albuminuria Screening (THOMAS) study, a randomized study investigating the feasibility of population screening for increased albuminuria by two different methods.

## Materials and methods

### Study setting and population

The THOMAS study is designed as an investigator-initiated, prospective, randomized population-based screening study. The University Medical Center Groningen, the Netherlands, acts as the coordinating center. Individuals from the general population are eligible if they are aged 45–80 years and living in the region of Breda, the Netherlands. Individuals are excluded when institutionalized. A random sample of men and women aged 45–80 years living in the region of Breda is drawn by Statistics Netherlands. This sample represents the Dutch population with respect to distribution of age, sex and socioeconomic class (as assessed by postal code area) [16]. The Dutch Ministry of the Interior and Kingdom Relations provides names, dates of birth, sex, and addresses.

### Study design and procedures

#### Study preparation, randomization, and recruitment

An overview of the study design is shown in Figs 1 and 2. Individuals are randomized in a 1:1 ratio to be invited for home-based screening for albuminuria with either a more conventional urine collection device (UCD) or a smartphone application (App). Randomization is performed by an independent clinical research organization that is unaware of the characteristics of the individuals that are assigned one of the two methods for home-based screening for albuminuria. A 4-block randomization method is used, with randomization performed in batches of 5,000 individuals. Individuals living in one household are randomized to the same group. A unique participant identification code is assigned to all participants. Due to the nature of the study and used study materials, blinding of the participants for the assigned screening method is not feasible.

**Fig 1 pone.0279321.g001:**
[figure not shown]
SPIRIT schedule of study procedures. Of note: Urinary sample collection includes the assessment albumin, creatinine and the ACR. Blood sample collection includes the assessment of HbA1c, glucose, total cholesterol, HDL cholesterol, LDL cholesterol, triglycerides, creatinine, and eGFR by CKD-EPI. Abbreviations: ACR, albumin-to-creatinine ratio; HDL, high-density lipoprotein; LDL; low-density lipoprotein; CKD-EPI, Chronic Kidney Disease Epidemiology Collaboration; CKD, chronic kidney disease; CVD, cardiovascular disease; GP, general practitioner; UCD, urinary collection device; App, smartphone application; EQ-5D, EuroQol 5D-5L.

**Fig 2 pone.0279321.g002:**
[figure not shown]
Study flow chart. Abbreviations: UCD, urinary collection device; App, smartphone application; ACR, albumin-to-creatinine ratio; CKD, chronic kidney disease; CVD, cardiovascular disease; GP, general practitioner.

Before the start of the study, GPs and nurse practitioners (NPs) in general practice working in the screening region were informed about the study. During the study, a regional GP specialized in CKD and CVD serves as contact person for GPs and NPs. A website (www.niercheck.nl), telephone number, and e-mail address are available for participants and healthcare professionals to provide information about the study and to answer questions. In order to increase reach among the population, study materials were tested by a panel of volunteers from a Dutch organization that assists in improving the understandability of official texts for subjects of low literacy (The ABC Foundation).

#### Home-based screening

All randomized individuals receive an invitation to participate in the home-based screening via mail, along with information on possible advantages and disadvantages of participation, and the assigned home-based screening method including test instructions. Participants are instructed to use midstream early morning void urine (EMV) for the test, and to postpone the home-based urine test in case of fever, urinary tract infection, pregnancy, menstruation, or having exercised intensively the day before. Two home-based albuminuria screening strategies are examined:

*UCD-method*. Individuals randomized to the UCD-method receive a PeeSpot UCD (Hessels+Grob B.V., Deventer, The Netherlands) [17,18]. This device consists of a holder containing a urine absorption pad in a transport tube (Fig 3). The urine absorption pad is a felt containing a dried hygroscopic polymer. Subjects hold the absorbent pad in their urine stream that absorbs approximately 1.2 ml of urine to collect a portion of urine. The participants insert the holder with the pad containing urine back into the tube, place the tube in a safety bag, and send this safety bag to a central laboratory by surface mail together with a signed informed consent form. A dried preservative in the urine absorption felt prevents bacterial growth during four days at room temperature. Participants are instructed to collect and send their urine sample on the same day, Monday through Thursday, and only during weather conditions that allow sending biosamples by mail (temperature between 0°C and 25°C). After receiving the sample in the central laboratory, the tube is centrifuged (5 minutes, 1800G) to release the urine into the tube with 100% albumin recovery. Urinary albumin and creatinine concentrations are measured by immuno-turbidimetry and enzymatically, respectively, on a cobas c502 analyzer (Roche Diagnostics, Almere, The Netherlands), with for albumin a lower limit of detection of 3 mg/L and intermediate precision of 4.2%, and for creatinine a lower limit of detection of 100 μmol/L and intermediate precision of 2.1%. ACR is reported as mg/mmol.

**Fig 3 pone.0279321.g003:**
[figure not shown]
Urine collection device and its components to be used in the UCD-method. Abbreviations: UCD, urinary collection device.

*App-method*. Individuals randomized to the App-method receive the ACR | EU test kit, a CE-marked home-based albuminuria screening self-test (Healthy.io Ltd, Tel Aviv-Yafo, Israel). This test kit contains a foldable urine cup, an ACR dipstick, an absorbing pad, a color board, and instructions to download a smartphone application (Fig 4). After providing digital informed consent, the App guides the user through the testing process step-by-step. Subjects first collect urine in the cup, in which they immerse the urine dipstick, of which the chemical pads change in color in response to the presence of albumin and creatinine. After the dipstick is placed on the color board, participants scan the dipstick with the App, which automatically makes a photo using the flashlight. The image is analyzed by an algorithm that uses the color board to calibrate for light conditions and color settings between different smartphone models. The App measures albumin at a concentration ≥ 6 mg/L as well as creatinine ≥ 0.06 g/L and returns results for the ACR following the KDIGO categorization: A1 (<30 mg/g, normal), A2 (30–300 mg/g, moderately increased), A3 (>300 mg/g, severely increased). This test result is directly shown to the participant in the App. Sensitivity and specificity for the home-based ACR | EU test are 98.4% and 92.9%, respectively, in a method comparison to the ACON U120 Ultra urine reagent strip analyzer (ACON Laboratories, San Diego, United States of America) that is routinely used in clinical chemistry labs.

**Fig 4 pone.0279321.g004:**
[figure not shown]
App test kit and its components to be used in the App-method. Abbreviations: App, smartphone application.

If the first test result is negative (ACR < 3 mg/mmol for the UCD-method; ACR <30 mg/g for the App-method), no further examinations are needed. However, if the first test result indicates increased albuminuria, participants are sent a second test kit for confirmation. When the result of the second test is negative, a third test is sent. In case the initial increased albuminuria result is confirmed by either the second or third test, the participant is invited for a visit to a screening facility where an elaborate screening follows. Reminders are sent to non-participating subjects three and six weeks after the initial invitations.

#### Elaborate screening

Participants are asked not to perform any strenuous physical activity on the day before the screening and to complete a questionnaire. During the elaborate screening visit, height, weight, and blood pressure are measured, blood is drawn, and a spot urine sample collected. Blood pressure (mm Hg) and heart rate are measured four times using an automatic device (OMRON M7; OMRON Healthcare, Hoofddorp, The Netherlands) in a seated position on the non-dominant arm, of which the average of the last three measurements is reported. HbA1c, glucose, lipid profile, and creatinine are assessed in the blood samples. In the urine sample, albumin and creatinine are measured, and the ACR is calculated. Leftover urine and blood are stored in a biobank. The time of urine and blood sampling as well as fasting state of the participant are reported. During the elaborate screening, an internist-nephrologist is available for urgent medical questions. An overview of the measurements performed at the elaborate screening is provided in Fig 1.

Risk factors are defined as abnormal in accordance with prevailing guidelines for Dutch GPs. Overweight is defined as a body mass index (BMI) >25 in case of age ≤70 years, and a BMI >28 in case of age >70 years. Hypertension is defined as a systolic blood pressure ≥140 mm Hg, diastolic blood pressure ≥90 mm Hg, and in case of a positive ACR, a systolic blood pressure ≥130 mm Hg and diastolic blood pressure ≥80 mm Hg [19]. Type 2 diabetes is defined as fasting plasma glucose ≥7.0 mmol/L, non-fasting plasma glucose ≥11.1 mmol/L, or a HbA1c ≥48 mmol/mol, (also in accordance with the American Diabetes Association (ADA) Guideline for diabetes [20]). For patients with known type 2 diabetes, inadequate regulation is defined as an HbA1c >53 mmol/mol in case of age <70 years, >58 mmol/mol in case of age >70 years and duration diabetes <10 years, and >64 mmol/mol in case of age >70 years and duration diabetes >10 years [19]. Prediabetes is defined as fasting plasma glucose of 5.6–6.9 mmol/L or HbA1c of 39–48 mmol/L in accordance with the ADA Guideline for diabetes [20]. An unfavorable lipid profile is defined as low-density lipoprotein (LDL) cholesterol >3.0 mmol/L in case of no other positive risk factors, >2.6 mmol/L in case of positive ACR or diabetes, or >1.8 mmol/L in case of cardiovascular disease history and age ≤70 years [21]. Impaired kidney function is defined as an eGFR (using the creatinine-based Chronic Kidney Disease Epidemiology (CKD-EPI) Collaboration equation) <60 ml/min/1.73 m^2^ [22,23].

Participants and their GP receive the results of the elaborate screening by mail. When abnormalities are found that warrant treatment according to the prevailing GP guidelines, participants are referred to their GP to be prescribed lifestyle measures (e.g., to lose weight and/or stop smoking) and/or medical intervention. This is also the case when participants are already known with having these risk factors, but appear to be poorly controlled. If no abnormalities are found other than albuminuria, participants receive a letter with the screening results and a recommendation to visit their GP one year later for repeat screening of albuminuria and CVD risk factors, again in accordance with prevailing guidelines.

Participants invited to the elaborate screening also receive a questionnaire to collect data on demographics (including educational and ethnic background), medical history (presence/history of CKD, hypertension, diabetes, hypercholesterolemia, and CVD), and medication use. Other topics addressed by this questionnaire are quality of life (EuroQoL 5D-5L [24,25]), usability of the screening strategy, health literacy (the All Aspects of Health Literacy Scale (AAHLS) [26]), and contact details of their GP and pharmacy.

#### Follow-up

After the screening period, the GPs and pharmacists of participants who receive the advice to contact their GP for prescription of lifestyle advice or medication will be approached to confirm whether the participant visited their GP within six months after the elaborate screening. If so, the GP/pharmacist is asked whether this visit to the GP had led to the start or change of treatment (lifestyle and/or medication) of CKD and CVD risk factors. Information from GPs and pharmacists will be collected via a questionnaire. All GPs and pharmacists of participants of the elaborate screening who provided informed consent for contacting the GP and pharmacy are approached.

#### Informed consent procedures

All participants have to provide informed consent upon participating in the screening. For the UCD-method, participants receive an informed consent form in the same postal package as their screening test, which they must fill out and send back via a return envelope. For the App-method, participants have to complete an informed consent form via the App they have downloaded. This procedure is executed with the help of a signing service provider. For authentication, participants must first fill in their name and e-mail address in the App. Subsequently, they have to agree with the conditions stated in the informed consent by clicking on an ‘I agree’ button. Subsequently, a PDF-file containing an electronic signature and details is sent via e-mail to the participants and a copy to the research team. After this procedure, participants can start the home-based screening test. For the elaborate screening, additional informed consent is requested for contacting the participants’ GP and pharmacy and for storing leftover blood and urine samples for future analyses.

### Outcomes

#### Primary outcomes

The primary outcomes are the participation rate and yield of the home-based screening, the elaborate screening, and the overall screening program (Fig 1). The outcomes will be assessed separately for each of the two home-based screening strategies. The participation rate is defined as the number of individuals completing the home-based screening, elaborate screening, and overall screening program relative to the number of invited individuals (with completion including the required confirmation tests). The yield of the home-based screening is defined as the number of individuals who test positive for albuminuria (at least two tests positive) relative to the number of participating individuals. The yield of the elaborate screening is determined as the number of participants with increased albuminuria and newly diagnosed or poorly controlled CVD or CKD risk factors (including hypertension, hypercholesterolemia, type 2 diabetes, and impaired kidney function.

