#### Sub-studies

Two sub-studies will be performed. The first sub-study will examine the false-negative rate for both home-based albuminuria screening strategies. Around 500 subjects per screening method who have a negative first home-based albuminuria screening test will be invited to perform an additional test, to examine the false-negative rate. This additional test will be done via the UCD, as this test provides a quantitative, exact ACR value as usual in clinical care. There is no need for further action, if this second test is also negative. If this second test is positive, the participant is sent a third test to confirm the result.

The second sub-study will examine whether lowering the cut-off value for the ACR increases the yield of the home-based screening. All subjects of the UCD-method with an ACR in their first test between 2–3 mg/mmol are invited for a second home-based albuminuria test (again with the UCD). If the ACR of the second test is negative (ACR <30 mg/g), there is no need for further action. If the ACR of the second test is positive (ACR ≥30 mg/g), the participant is invited for a third home-based test. If the third test is negative, no further action is undertaken. If the ACR of the third test is positive, the participant is invited for the elaborate screening.

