### Sample size

The sample size of this study is calculated to be able to show a 5% difference in participation rate between the two screening strategies, with assumptions based on previous data [7], including an overall participation rate for the home-based screening of 50%, 8% of the participants having elevated ACR, of which 90% will be confirmed by the confirmatory tests, and a participation rate in the elaborate screening of 90%. Adopting a power of 80% and a 2-sided alpha of 0.05, a minimum of 15.032 individuals are to be invited to participate to detect this 5% difference in participation rate between the two screening strategies. This number of individuals also allows discerning a significant difference between both screening strategies in the number of individuals with elevated albuminuria diagnosed with at least one newly discovered CKD or CVD risk factor.

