### Statistical analyses

The statistical package IBM SPSS (version 23, Armonk, NY) will be used for the analysis of the data. Baseline characteristics for continuous variables will be expressed as mean and standard deviation for continuous variables in case of normal distribution, and as median and interquartile range in case of non-normal distribution. Discrete variables will be reported as number and proportions. The primary outcomes, participation rate and yield of screening, will be compared between the two treatment strategies using the Chi-square test. Participation and completion rates will be presented for the intention-to-screen population. Yield of screening will be presented for the intention-to-screen population as well as the per-protocol population. Characteristics of participants and non-responders will be compared using univariable and multivariable logistic regression models. Cost-effectiveness will be assessed using an individual-level health state transition model (microsimulation), comparing the two screening strategies with usual care (no screening). It will be carried out from a Dutch healthcare perspective and the model will be run over the remaining lifetime. Data from literature will be used to estimate participants quality of life, costs of interventions after the elaborate screening, the efficacy of interventions to prevent CVD and CKD progression, and the costs associated with CVD and CKD events. Effectiveness will be calculated expressed in total costs and total effects (in QALYs) per screening method. Incremental effects will be calculated and the incremental cost-effectiveness ratio (ICER), will be determined, defined as incremental costs divided by incremental gain in QALYs.

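### The primary home-based yield is scored on each arm's own test, so a difference between arms may reflect recurring App false positives or the lower UCD cut-off; the visit ACR is not used to tell these apart

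*Protocol article*

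**What the plan says.** *Primary outcomes* (Protocol article) fixes the measure: "The yield of the home-based screening is defined as the number of individuals who test positive for albuminuria (at least two tests positive", with participants as denominator. *Home-based screening* gives the test behind it. In the UCD arm it is laboratory immuno-turbidimetry with a cut-off of 3 mg/mmol. In the App arm it is a dipstick read by phone and returned as a category with a cut-off of 30 mg/g. App sensitivity and specificity are given as "98.4% and 92.9%, respectively, in a method comparison to the ACON U120 Ultra urine reagent strip analyzer". After a positive first result, "participants are sent a second test kit for confirmation", with a third if the second is negative. No change of method is mentioned for these kits, so I read them as the arm's own test.

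*Statistical analyses* fixes the comparison: "The primary outcomes, participation rate and yield of screening, will be compared between the two treatment strategies using the Chi-square test".

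Three further passages bear on error:

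- *Sub-studies*: "The first sub-study will examine the false-negative rate for both home-based albuminuria screening strategies". About 500 first-test negatives per arm are retested with the UCD. Positives get no matching check.
- *Elaborate screening*: "In the urine sample, albumin and creatinine are measured, and the ACR is calculated". This applies to attendees of both arms. The same section lowers the hypertension threshold "in case of a positive ACR, a systolic blood pressure ≥130 mm Hg and diastolic blood pressure ≥80 mm Hg", without saying whether the home or the visit result counts.
- *Discussion*: repeat testing is relied on to limit false positives, and re-expressing UCD results in mg/g is offered as an option after the study.

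The elaborate-screening yield in *Primary outcomes* requires increased albuminuria plus a risk factor, again without saying which ACR decides.

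**The concern.** Two assays with different error rates and different cut-offs feed one between-arm comparison. Requiring a second positive removes errors that vary from test to test. It does not remove an error that recurs in the same person. Such errors count as detections in the App arm, so a less specific App could score a higher yield without finding more albuminuria. The UCD cut-off, lower when put in the same units, raises the UCD yield and can hide this or produce a difference of its own.

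The safeguards leave a gap. The sub-study looks only at negatives. The optional mg/g conversion aligns the cut-off but not assay error. The visit ACR could separate the two, but no yield definition names it.

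At stake is the yield comparison, which the Discussion lists with user-friendliness, participation and cost-effectiveness as grounds for choosing a method. The sample size is built on participation, and the participation comparison does not suffer.

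**Working it through.** **Inputs from the plan.** 15,032 invited, 1:1, 50% participation, 8% with elevated ACR, 90% of these confirmed, 90% visit attendance (*Sample size*); App sensitivity 98.4% and specificity 92.9% (*App-method*); first test positive, then second or third positive (*Home-based screening*). I take 15,032 as stated; how it was derived is a separate matter.

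**The plan's own funnel.** 15,032 × 0.5 = 7,516 participants; × 0.08 = 601 positive; × 0.90 = 541 confirmed, which is 7.2% of participants. Per arm: 3,758 participants and 0.072 × 3,758 = 271 confirmed.

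**Assumptions.** The 7.2% are true cases in both arms. The UCD makes no errors. The App specificity, measured against another strip analyser, carries over to a laboratory ACR. Let *r* be the probability that a false first positive is confirmed by test two or three. With independent errors, *r* = 1 − spec².

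**App yield.**

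- True confirmed: 0.072 × 0.984 × (1 − 0.016²) = 0.0708 (266 people).
- False confirmed: 0.928 × (1 − spec) × *r*.
- Chance of a spurious App advantage: Φ((d − 1.96·s₀)/s₁), where d is the yield difference and s₀ and s₁ are its standard errors under no difference and under the assumed yields.

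First row as an example: *r* = 1 − 0.929² = 0.137; false = 0.928 × 0.071 × 0.137 = 0.0090 (34 people, 11% of App detections); d = 0.0799 − 0.072 = 0.0079; s₀ ≈ s₁ ≈ 0.0061; Φ(−0.67) = 0.25.

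| Specificity | *r* | False App detections | App yield v UCD 7.2% | Chance App called higher |
|---|---|---|---|---|
| 92.9% | 0.137 (independent) | 34 | 8.0% | 25% |
| 92.9% | 0.25 (assumed) | 62 | 8.7% | 69% |
| 92.9% | 0.5 (assumed) | 124 | 10.4% | over 99% |
| 98% (assumed) | 0.040 (independent) | 3 | 7.2% | 2% |
| 98% (assumed) | 0.5 (assumed) | 35 | 8.0% | 26% |

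**Cut-off offset.** With creatinine at 113.12 g/mol, 3 mg/mmol = 3 / 0.11312 = 26.5 mg/g. Suppose 0.5 or 1.0 points of UCD participants are confirmed only because of this (assumption), so that the UCD yield is 7.7% or 8.2%.

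- 92.9%, independent errors: difference +0.3 or −0.2 points; chance of an App advantage 7% or 1%.
- 92.9%, *r* = 0.5: +2.7 or +2.2 points; 98% or 90%.
- 98%, independent errors, offset 1.0: 7.16% v 8.2%, d = −0.0104, s₀ ≈ s₁ ≈ 0.0061; the UCD is called higher with probability Φ((0.0104 − 0.0120)/0.0061) ≈ 0.40, from the cut-off alone.

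**What the visit ACR could add.** Assume 90% attend, 90% of true cases and 0–10% of false detections reach 30 mg/g at the visit, and home results are first aligned at 30 mg/g.

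- Verified yield, UCD: 0.9 × 0.072 × 0.9 = 5.8%.
- Verified yield, App: 5.7–5.8% with independent errors, 5.7–6.0% with *r* = 0.5. The chance of a spurious App advantage falls to about 2%, and to 2–6% with *r* = 0.5.
- Home-confirmed attendees below 30 mg/g, independent errors: 10% of 244 (UCD) v 19–20% of 270 (App).
- Without alignment, taking 0–10% of offset cases to verify, the UCD share becomes (0.072 × 0.1 + 0.005 × 0.9 to 1.0) / 0.077 = 15–16%, or 20–21% at an offset of 1.0 point. The contrast shrinks or disappears.
- True cases left unverified: 1 − 0.9 × 0.9 = 19%.

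**The case against.** **Counting what each strategy flags is legitimate.** Home positivity drives visits and costs, and its definition is clear. This stands, and it is why the measure should stay.

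**The article already handles part of this.** A second positive is required, the cut-off mismatch is disclosed, and the elaborate-screening yield also demands a risk factor. Each protection is partial. Recurring errors pass the second test. The conversion is optional and concerns only the cut-off. The elaborate yield does not say which ACR decides.

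**A visit-ACR analysis could sit in documents not shown.** It could. But the article itself fixes both the own-test definition and the Chi-square comparison, and the point rests on those.

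**The size is not documented.** This stands. No passage gives the repeat rate, and 92.9% is agreement with another strip analyser. A reader might infer that the App will produce a spurious advantage, or that 7.1% of unaffected App participants will be counted as detections. The documents support neither. Confirmation removes most independent errors, and the offset can cancel the rest.

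**The visit ACR is an imperfect reference.** Also true. It is one spot sample in attendees only, and the Discussion rates random spot ACR below early morning void. A reader might infer from 10% v 19–20% that the visit check would reliably expose App errors. I make no such power claim. With no offset, power is 55–66% if only 80% of true cases verify. Unaligned, with 90% verifying and the same 0–10% of offset cases and false detections verifying, it is about 22–25% at an offset of 0.5 points and about 1% at 1.0 point.

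**Conclusion.** The point holds in a limited form. As defined, a between-arm difference in home-based yield cannot be read as a difference in albuminuria found, because recurring App false positives and the lower UCD cut-off both enter it, usually in opposite directions. The plan checks false negatives but names no use of the visit ACR to check false positives.

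The size is unknown. Under the stated assumptions the App excess runs from about 0.8 points with independent errors to about 3 points if half of false positives repeat. It is negligible at 98% specificity with independent errors. The upper figures depend on an assumed repeat rate. The documents do not show that the yield comparison will mislead, and they give no reason to replace the primary outcome.

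**What to change.** 1. Keep the primary measure and describe it in *Primary outcomes* as confirmed home-test positivity.
2. Make the re-scoring of UCD home results at 30 mg/g a planned analysis. State a rule for UCD participants whose second result falls between the two cut-offs: the third kit that a 30 mg/g rule would have triggered was not sent.
3. Add to *Primary outcomes* and *Statistical analyses* a supporting visit-verified yield: home-confirmed at 30 mg/g in both arms and visit ACR at or above 30 mg/g, relative to participants, compared by Chi-square.
4. Report by arm the attendance, the verified share among attendees, and the share of home-confirmed attendees with visit ACR below 30 mg/g. Limit UCD attendees to those confirmed at 30 mg/g, so that the cut-off offset is not mixed with assay error.
5. State which ACR decides *increased albuminuria* in the elaborate-screening yield and *positive ACR* in the risk-factor definitions, and repeat that yield with the visit ACR deciding.
6. Say in the Discussion that the choice of method is read on both yields.

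The cost is definitions and tabulations of results already collected: no new samples, kits or visits, and no change of primary outcome while data collection is ongoing. The downside is that some true cases stay unverified (about 19% under the assumptions above) and differing attendance can shift the verified yield, so it must be shown beside the primary measure and the share among attendees.
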